   1. PRIMARY OUTCOME

The primary outcome will be duration (in hours) between study inclusion and successful extubation (defined by the absence of reintubation or death within the 7 days (168 hours) following extubation). Reintubation and resuming of mechanical ventilation for less than 24h related to unplanned surgical procedure will not be considered as extubation failure. Patients extubated but exiting ICU within the 7 days following extubation will be considered as successful extubation. In patients not meeting extubation success criteria, data will be censored at day-90 or date of death whichever comes first.

- 1. SECONDARY PARAMETERS OUTCOMES

1. Rate of first successful extubation: number of patients successfully extubated after their first extubation/total number of patients per group
2. Invasive mechanical ventilation duration (expressed in hours): total cumulative time spent on invasive mechanical ventilation since inclusion per group. Each time period spent on invasive mechanical ventilation from inclusion until successful extubation are summed up. Patients not experiencing successful extubation will be censored at Day 90 or time of death (if earlier than Day 90).
3. Mechanical (invasive and non-invasive) ventilation duration (expressed in hours): total cumulative time spent on invasive and non-invasive mechanical ventilation since inclusion per group.
   - If the patient is successfully extubated with post-extubation NIV: date/time of NIV cessation minus date/time of inclusion. (or date/time of ICU discharge If NIV not ceased at ICU discharge)
   - If the patient is successfully extubated without post-extubation NIV: date/time of successful extubation minus date/time of inclusion.
   - Patients not experiencing successful extubation will be censored at Day 90 or time of death (if earlier than Day 90).
4. Ventilator-free days (VFD) at Day-28 and Day-90. VFD will be computed as follows from the day of inclusion:
   - VFD = 0 if the patient dies between inclusion and day-28 for VFD at day-28, or if the patient dies between inclusion and day-90 for VFD at day-90

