   1. GENERAL METHODOLOGY

Quantitative variables will be will be described using the following statistics: number of missing data, mean, standard deviation, quartiles, minimum and maximum values, number and rate of missing variables, and compared between groups with the Mann-Whitney test. No normality check will be performed. Qualitative variables will be reported as absolute and relative frequencies, number and rate of missing variables, and compared between groups with the chi-2 test or the Fisher exact test. Variables will be compared between both groups, except for specific analysis described in 5.2. We will not adjust p-value for multiple comparison. Univariable absolute difference will be reported for each variable as difference [95% confidence interval]. The Hodges-Lehmann method will be used to compute unbiased median differences for outcomes and their CI95%. For qualitative variables, 95% confidence interval will be computed through bootstrapping.

P-value <0,05 with a bilateral hypothesis will be considered as significant. All the analyses will be carried out using R for Windows.

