  1. PRIMARY DATA ANALYSES

5.2.1 Outcome variables

5.2.1.1 Primary outcome

Primary outcome (time to successful extubation) is subjected to competitive risk (death). However, assuming competing risk will be identical in both groups, survival analysis will be done according to a cause-specific analysis (Cox model) with randomization strata as covariate. Hence, primary outcome will be assessed with the Hazard Ratio (HR) produced by Cox model.

Time to event will be:

- For patients successfully extubated: time from inclusion to successful extubation
- For patients who died before successful extubation or Day 90: time from inclusion to death, with censoring at this time point
- For patients not weaned from mechanical ventilation at Day 90 will be censored at this time point.

Two diagnosis will be performed:

1. Proportional hazard assumption will be checked through scaled Schoenfeld residuals statistical test and graphical plot
2. Verification of influential observations: outliers will be identified by 1) plotting deviance residuals and checking symmetrical distribution around zero and 2) plotting the estimated changes in the regression coefficients upon deleting each observation in turn (dfbeta) . In case of influential observation, the observation will be checked for error, corrected if wrong, or conserved if true.

If the proportional hazard assumption is not met, a chronological variable will be used, if possible, otherwise, a log-rank test will be performed.

To account for competing risk, a sensitivity analysis will be performed on the main outcome as follows: the main outcome will be described with cumulative incidence functions and analyzed with a Fine and Gray model with successful extubation as event and death as competitive risk, with randomization strata as covariate. Proportional hazard assumption will be checked by plotting Schoenfeld residuals against event time for each covariate. If the proportional hazard assumption is not met, a chronological variable will be used, if possible.

We will provide graphical representation using a Kaplan Meier curve for the Cox model, depicting the two groups without stratification and a cumulative incidence graph for Fine and Gray model depicting the two groups without stratification, with successful extubation and death as events.

Results will be reported a table with four columns (intervention group, control group, Hazard ratio, p-value). The subgroup analysis will be presented as a forest plot.

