In order to express effect size, the median value of the difference between groups in time to successful extubation will be provided (along with its 95% confidence interval).

A second statistician will carry out the analysis of the primary outcome on the dataset.

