5.2.1.2 Secondary outcomes

Analysis will be carried out as described in 5.1. Results will be reported a table with four columns (intervention group, control group, univariable absolute difference with 95% confidence interval, p-value).

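### Ventilation durations are defined as censored at death or day 90, but are assigned a rank test and a Hodges-Lehmann estimate that cannot use censoring

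*Protocol*

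**What the plan says.** Section 4.2, item 2, defines invasive ventilation duration as the "total cumulative time spent on invasive mechanical ventilation since inclusion per group". Item 3 does the same for invasive plus non-invasive ventilation. Both items carry the rule "Patients not experiencing successful extubation will be censored at Day 90 or time of death (if earlier than Day 90".

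For the analysis of secondary outcomes, section 5.2.1.2 says only "Analysis will be carried out as described in 5.1". Under section 5.1, quantitative variables are "compared between groups with the Mann-Whitney test", and "The Hodges-Lehmann method will be used to compute unbiased median differences for outcomes and their CI95". Section 5.1 allows exceptions for specific analyses set out in section 5.2, but section 5.2 gives none for these durations.

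Two other outcomes are handled differently:
- Primary outcome (section 5.2.1.1): "survival analysis will be done according to a cause-specific analysis (Cox model) with randomization strata as covariate", with a Fine and Gray sensitivity analysis.
- Ventilator-free days (section 4.2, item 4): death takes the worst value, "VFD = 0 if the patient dies between inclusion and day-28 for VFD at day-28".

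**The concern.** The definition and the analysis do not fit together. A censored duration means that the true value is at least the recorded one. Mann-Whitney and Hodges-Lehmann have no place for a censoring indicator, so they read the recorded time as the completed duration. A patient who dies ventilated at 40 h is then ranked ahead of a patient extubated alive at 60 h.

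The other available reading does not help. If censored values are coded as missing and left unimputed, as the missing-data paragraph of section 5.1 provides, the comparison is confined to successfully extubated patients, a subset formed after randomization.

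This is not a detail left for a later analysis plan, because the protocol itself names the method. At stake are secondary objectives 2 and 3, each judged at a two-sided 5% level. If the arms differ in mortality, a difference in deaths can be reported as a difference in ventilation time.

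**Working it through.** **Design figures (section 2.5).** With HR 2, two-sided 5% and 80% power, Schoenfeld's formula gives 4 × (1.960 + 0.842)² / (ln 2)² = 65.3, so 66 events. Inflation gives 66 / (1 − 0.30) = 94.3, against 94 stated. Both reproduce. The 30% is the assumed share without successful extubation, from death and weaning failure together: 0.30 × 94 = 28.2, so about 28 patients could have a censored duration. The protocol does not give the share of deaths alone, nor any planning figure for outcomes 2 and 3.

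**Direction of the bias.** Let d₁ and d₀ be the proportions dying before extubation in the two arms. Let extubation times be identical in both arms, and let q be the probability that a death time is shorter than an extubation time. If death times are entered as durations, the probability that a random patient in arm 1 has a shorter value than one in arm 0 is

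(1−d₁)(1−d₀)/2 + d₁(1−d₀)q + (1−d₁)d₀(1−q) + d₁d₀/2 = 0.5 + (d₁ − d₀)(q − 0.5).

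The test should be centred on 0.5. With d₁ = d₀ it is. Otherwise arm 1 looks better when q > 0.5 (deaths come early) and worse when q < 0.5 (deaths come late).

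**Size.** Inputs:
- 47 per arm, from section 2.5.
- Median extubation time 46 h in both arms: the pilot median of 22 h plus the 24 h difference in section 2.5. Those times run from the first SBT, so using them for ventilation duration from inclusion is an assumption.
- Deaths of 30% against 10%, exponential times and the median death times below are assumptions.

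For exponential times, q = 46 / (46 + median death time). Simulation results, 1,000 runs per row, two-sided Mann-Whitney at 5%:

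| Median death time | q | 0.5 + 0.20(q − 0.5) | Significant for the arm with more deaths | Significant against it | Median Hodges-Lehmann difference |
|---|---|---|---|---|---|
| 12 h | 0.793 | 0.559 | 15.4% | 0% | −6.4 h |
| 24 h | 0.657 | 0.531 | 8.1% | 0.5% | −4.1 h |
| 48 h | 0.489 | 0.498 | 2.2% | 2.5% | about 0 h |
| 120 h | 0.277 | 0.455 | 0.2% | 10.6% | +6.8 h |

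The nominal rate in each direction is 2.5%. A repeat with 4,000 runs gave 16.1%, 7.0% and 2.7% in favour at 12, 24 and 48 h, and 11.4% against at 120 h. With 15% deaths in each arm, each direction stayed between 2% and 3%.

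**Worst rank for death or no extubation by day 90.** This sets q = 0, and the formula gives 0.5 − 0.20 × 0.5 = 0.40 whatever the death time. In simulation, 37% to 39% of trials were significant against the arm with more deaths and at most 0.1% in its favour.

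**Sensitivity to the time scale.** With log-normal durations (log-SD 1), death times uniform on 12-120 h that cut the duration short, and deaths of 30/15% and 30/10%, false benefit is:
- 11.1% and 15.0% at an assumed median of 120 h;
- 4.5% and 5.7% at 46 h;
- 2.7% and 3.3% at 22 h.

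**The case against.** The case for leaving the plan alone has real content.

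- **The direction is conditional.** A reader might infer that any strategy with more deaths will appear to shorten ventilation. The algebra does not support that: late deaths push the comparison the other way. False-benefit rates of 11-15% under the log-normal set-up need an assumed median of 120 h, well above the 22 h and 46 h that follow from section 2.5. This stands.
- **Equal mortality.** Section 5.2.1.1 assumes that the competing risk is the same in both groups, and then the error rate holds. But that is an assumption about a trial result, and the protocol does not rely on it alone for the primary outcome, where it adds a Fine and Gray analysis.
- **The 30% is not a death rate.** It includes weaning failures. Those still ventilated at day 90 receive a very long value, which is not favourable. This stands, and is why the mortality figures above are only assumptions.
- **Mortality and ventilator-free days are reported alongside.** They would help a reader notice an artefact. They do not correct the p-values or estimates for outcomes 2 and 3.
- **ICU and hospital stay.** A reader might call these the same error. Section 4.2 does not define them as censored and gives no value for a death, so what is missing is a rule; there is no contradiction.
- **Primary effect size.** Section 5.2.1.1 says that "the median value of the difference between groups in time to successful extubation will be provided" but names no estimator. A reader might infer Hodges-Lehmann from section 5.1. That is possible, but the document does not say so.

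**Conclusion.** Wrong as written for secondary outcomes 2 and 3, and should be fixed. The protocol's stated test and estimator cannot carry out its own censoring rule. With unequal mortality the comparison is biased, and the sign depends on the timing of deaths. Under assumed deaths of 30% against 10% and a 46 h median, false benefit for the arm with more deaths runs from about 15-16% of trials (median death time 12 h) through 7-8% (24 h) to nominal (48 h). At 120 h about 11% of trials are significant against that arm. The mortality rates, death times and distributions are assumptions; the mismatch itself is in the text and needs none of them.

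The point does not reach the primary Cox test, the 66 events or the 94 patients. Because the affected analyses are secondary and mortality is reported beside them, it need not block the trial. For ICU and hospital stay the finding is limited to the missing death rule, and for the primary median difference to the unnamed estimator.

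**What to change.** For outcomes 2 and 3, state one of the following in section 5.2.1.2 before unblinded analysis:

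1. Keep Mann-Whitney and Hodges-Lehmann, but give death before successful extubation the worst rank, in line with the zero score in ventilator-free days. Say how patients still ventilated at day 90 rank against deaths, and label the result as a composite of death and duration.
2. Analyse time to liberation alive with death as competing event, using the methods already in section 5.2.1.1. For outcome 2 this largely repeats the primary endpoint, since the summed ventilation periods are no longer what is analysed.

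State the same death rule for ICU and hospital stay. For the primary median difference, name the estimator. If Hodges-Lehmann was intended, replace it with one that respects censoring, such as the difference in medians read from the cumulative incidence curves with a bootstrap interval.

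Cost: wording only, since extubation and death times are already needed for the primary outcome. Worst rank has a price in power when many patients die at equal rates. In simulations with medians of 22 h and 46 h and median death times of 24 to 240 h, significance in favour of the faster arm fell from 64-70% to 55-57% with 15% deaths per arm, and from 37-56% to 29-32% with 30%. That is a reason to choose the rule deliberately and in advance.

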   - VFD = 28-x for VFD at day-28 or VFD = 90-x for VFD at day-90 if the patient is successfully weaned from invasive mechanical ventilation, with x being the number of days from inclusion to last successful extubation. Successful weaning from mechanical ventilation will be defined as extubation without reintubation within at least 7 days (or weaning from mechanical ventilation for at least 7 days for patients with tracheostomy)
   - VFD = 0 if the patient is mechanically ventilated for more than 28 days after inclusion for VFD at day-28, or more than 90 days after inclusion for VFD at day-90
5. ICU stay (days): ICU length of stay between inclusion and ICU discharge
6. Hospital stay (days): hospital length of stay between inclusion and hospital discharge (to home or rehabilitation facility).
7. ICU, day-28, and day-90 mortality: defined as the ratio of the number of death over each period over the total number of patients per group.
8. Reintubation rate: number of patients with any reintubation divided by the number of patients per group

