**TERTIARY OUTCOMES**

- Tracheostomy during ICU stay: categorical variable: Yes or no
  - Time of tracheostomy: date variable. Expressed as date (DD/MM/YYYY) and hour (HH:MM)
  - Method of tracheostomy: categorical variable. Percutaneous or surgical
  - Indication(s) for tracheostomy: categorical variable:
    - Difficult weaning: yes or no
    - Swallowing disorder/abundant bronchial secretions: yes or no
    - Other: yes or no
  - Patient successfully weaned from ventilation: yes or no
    - If yes: Time of successful weaning: date variable. Expressed as date (DD/MM/YYYY) and hour (HH:MM)
- End of protocol: categorical variable. Secondary exclusion or end of protocol
  - Date of study end: date variable. Expressed as date (DD/MM/YYYY)
  - In case of secondary exclusion: categorical variable. Transfer to another ICU not participating to the study; Consent withdrawal; In case of serious adverse event, according to the clinician in charge.
  - In case of end of protocol (Cause of end of protocol): categorical variable. No reintubation in the 7 days following extubation; Withdrawing of care or withholding of reintubation decision; ICU discharge ; death ; patient still intubated at Day 90.
- Severe adverse event: categorical variable. Yes or no.
- Respiratory status at ICU discharge (Day 28, Day 90): categorical variable. Not ventilated, non-invasive ventilation (except CPAP), invasive ventilation (tracheostomy), invasive ventilation (intubated), tracheostomy (without ventilation), dead, lost to follow up
- Date of ICU discharge: date variable. Expressed as date (DD/MM/YYYY)
- Date of hospital discharge: date variable. Expressed as date (DD/MM/YYYY)
- Successful extubation: categorical variable. Yes, death or weaning failure
- Successful extubation rank. Discrete variable. NA in case of death
- Time of successful extubation: date variable. Expressed as date (DD/MM/YYYY) and hour (HH:MM).
- Number of reintubation: Discrete variable

1. Statistical Methodology

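### A tracheostomised survivor already off the ventilator is run to day 90 in secondary outcome 3 (and in outcome 2 on one reading), although VFD counts the same patient as weaned

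*Protocol*

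**What the plan says.** All references are to the Protocol.

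- **4.1** defines the event as "successful extubation (defined by the absence of reintubation or death within the 7 days (168 hours) following extubation". There is no route to this event through a tracheostomy.
- **4.2, item 2** (invasive ventilation) is a cumulative time: "Each time period spent on invasive mechanical ventilation from inclusion until successful extubation are summed up". **Item 3** (invasive plus non-invasive) is also described as cumulative time, but its branches are computed as elapsed time, for example "date/time of successful extubation minus date/time of inclusion". Both items end with the same rule: "Patients not experiencing successful extubation will be censored at Day 90 or time of death (if earlier than Day 90".
- **4.2, item 4** (VFD) has a tracheostomy clause in its definition of successful weaning: "or weaning from mechanical ventilation for at least 7 days for patients with tracheostomy". It computes 28-x or 90-x, "with x being the number of days from inclusion to last successful extubation".
- **4.3, Tertiary outcomes**, records for tracheostomised patients whether they were weaned and, if so, "Time of successful weaning: date variable", with hour and minute.
- **5.2.1.2** sends the secondary outcomes to **5.1**: mean, SD, quartiles, minimum and maximum, the Mann-Whitney test and Hodges-Lehmann differences.
- **5.2.1.1**, third time-to-event category: "For patients not weaned from mechanical ventilation at Day 90 will be censored at this time point".

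**The concern.** Tracheostomy at entry is an exclusion criterion (2.3), so the patients in question receive one after inclusion, come off the ventilator and survive. The plan foresees them: it lists difficult weaning as a tracheostomy indication and collects the time of weaning. Yet items 2 and 3 have no clause for them, and item 4 has one that cannot be computed as written.

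The same patient can then be a 90-day ventilation case in one row of the results table and have many ventilator-free days in another. Read strictly, x is undefined, and because missing data are not imputed the patient could also drop out of VFD. If the rule is settled only during analysis, the choice is made after the fact in an open-label trial.

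**Working it through.** **Inputs.** From the Protocol: horizon 90 days = 90 × 24 = 2160 h; 47 patients per arm; the rules above. Assumed, because the Protocol gives no figure: the weaning day w, continuous ventilation from inclusion to day w, and survival to day 90.

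**Step 1. Apply the rules to one patient.**

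- Item 3 as written: no successful extubation and no death, so the value is 2160 h for every w.
- Item 3 ended at the recorded weaning time: 24w h.
- Excess: (90 − w) × 24 h.
- VFD with x read as w: VFD-90 = 90 − w; VFD-28 = 28 − w, or 0 if w is above 28.

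| w (assumed) | As written (h) | To weaning (h) | Excess (h) | VFD-90 | VFD-28 |
|---|---|---|---|---|---|
| 10 | 2160 | 240 | 1920 | 80 | 18 |
| 20 | 2160 | 480 | 1680 | 70 | 8 |
| 40 | 2160 | 960 | 1200 | 50 | 0 |
| 60 | 2160 | 1440 | 720 | 30 | 0 |

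A duration of 2160 h implies no ventilator-free time in 90 days, which contradicts the VFD-90 column in every row.

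**Step 2. Does censoring rescue the value?** Only if the analysis uses the censoring indicator. The summaries and tests in 5.1 do not, so 2160 h is handled as an observed duration.

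**Step 3. Item 2.** It sums periods actually spent on invasive ventilation. If day 90 only closes the observation window, the patient weaned on day 20 contributes the true 480 h. If day 90 is the assigned value, as in item 3, the patient contributes 2160 h. The text does not choose.

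**Step 4. Effect on an arm mean.** One such patient with w = 20 raises the mean by 1680 / 47 = 35.7 h.

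**Step 5. Effect on the test (illustration only).** A simulation took 47 per arm, both arms exponential with median 60 h, and weaning of tracheostomised patients uniform on days 10 to 40 (mean day 25).

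| Weaned with tracheostomy, by arm | Mean difference, true times | Mean difference, day-90 rule | Mann-Whitney rejection, true times | Mann-Whitney rejection, day-90 rule |
|---|---|---|---|---|
| 7 v 2 | 54 h | 221 h | 0.104 | 0.106 |
| 5 v 2 | 32 h | 132 h | 0.049 | 0.050 |

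The shift agrees with direct arithmetic: (7 − 2) × (90 − 25) × 24 / 47 = 166 h and (5 − 2) × 1560 / 47 = 100 h. The rank test hardly moves because these patients rank near the top under either rule.

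**Step 6. Sample size (2.5).** Schoenfeld's formula with hazard ratio 2, two-sided 5%, 80% power and 1:1 allocation gives 66 events, as stated. 66 / 0.70 = 94.3, against 94 stated. Neither figure depends on this point.

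**The case against.** The strongest reply is that the text says censored, not ventilated, until day 90, and that both items are described as time spent on ventilation. For item 2 this stands: summing actual periods gives the right hours. A reader might infer that both outcomes unambiguously count these patients as ventilated to day 90, and for item 2 the document does not support that. For item 3 the reply is weak, because its other branches use elapsed time and the analysis makes no use of censoring.

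Other stronger readings also fail:

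- **That a tested conclusion changes.** The mean is descriptive here. Inference rests on Mann-Whitney, which hardly moves in the illustration. Medians should be similarly stable while such patients are few.
- **That the shift should be judged against 24 h.** That figure in 2.5 is the relevant difference for the primary outcome and is tied to a ratio of medians. It is not a yardstick for a mean of a secondary outcome.
- **That a sizeable share of an arm is affected, or that the arms differ.** The Protocol gives no number. The 30% in 2.5 pools deaths with weaning failures, and 5.2.5 allows for fewer than 5 tracheostomies by planning to report them in text in that case. Differential use is possible in an open trial, but nothing in the document shows it.
- **That the primary analysis is left undefined.** The third category in 5.2.1.1 is loosely worded and does not fit a weaned tracheostomised survivor. However, 4.1 already censors at day 90 or death everyone who does not meet the extubation success criteria.

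It is also fair to say that x in VFD can sensibly be read as the weaning date, given the tracheostomy clause beside it. The literal definition still points elsewhere.

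**Conclusion.** The point holds for item 3, for item 2 on one of its two readings, and for the definition of x in VFD. A stated rule gives a surviving tracheostomised patient a duration that contradicts both the outcome's own description and that patient's VFD. The excess is (90 − w) × 24 h per patient: 1680 h if weaned on day 20, and 720 to 1920 h for w from 60 down to 10. These values of w are assumptions.

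Reported means, SDs and maxima of the duration outcomes are exposed. Medians and the Mann-Whitney comparison are hardly affected, and the primary result and sample size are not. The number of patients is unknown and may be small. This is a modest definitional fault in secondary outcomes, worth correcting because the correction is nearly free.

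**What to change.** 1. **Item 3:** for tracheostomised patients, end ventilation at the recorded date and time of successful weaning, defined as the start of the period of at least 7 days off the ventilator.
2. **Item 2:** state that only periods actually spent on invasive ventilation are summed, up to successful extubation or, with tracheostomy, up to that same weaning time.
3. **Item 4:** define x as days from inclusion to last successful extubation or, with tracheostomy, to that weaning time.
4. **5.2.1.1, wording only:** make the third category *not successfully extubated by Day 90*, as 4.1 already requires.

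The cost is four short wording changes. The weaning date and hour are already listed among the collected variables.

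There is one downside. The schedule in 2.6 places tracheostomy and ventilation-cessation data at ICU discharge or death, with only respiratory status and mortality at days 28 and 90. Weaning after ICU discharge may therefore lack an exact time. For those few patients, keep censoring at day 90 or at last known status, and report how many there are.

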**DAILY ASSESSMENTS**

These variables will be collected from Day 1 until Day 90:

- If the patient is intubated (SBT data):
  - Preliminary weaning criteria: categorical variable. Present or absent.
  - SBT result: categorical variable. Success or failure.
  - Arterial blood gas in case of SBT success:
    - pH: continuous variable. Expressed without unit, with a precision of 0.01
    - PaCO2: continuous variable. Expressed in mmHg, as an integer
    - PaO2: continuous variable. Expressed in mmHg, as an integer
    - FiO2: continuous variable. Expressed in %, as an integer. For control group, FiO2 is equal to 21+ 3*O2 flow on T-piece
  - Cough score: categorical variable. 0, 1, 2, 3, 4, 5
  - Abundance of respiratory secretions: categorical variable. 0, 1, 2, 3, 4
  - For intervention group: result of SBT-TP, categorical variable. Success or failure.
  - Summary of extubability criteria
    - Acceptable cough (cough score ≥3): categorical variable. Yes or No
    - Acceptable respiratory secretions (abundance of respiratory secretions ≤2): categorical variable. Yes or No
    - No general anaesthesia planned on the next 24h: categorical variable. Yes or No
    - No argument for laryngeal obstruction: categorical variable. Yes or No
    - Number of positive extubability criteria: numerical variable. Ranging from 0 to 4
  - Date (JJ/MM/AAAA)
  - Hour of extubation (HH:MM)
- If the patient is extubated (extubation data):
  - Patient extubated today: categorical variable. Yes or no
  - Extubation type: categorical variable. Programmed extubation per protocol; programmed extubation (protocol violation) or auto-extubation
  - Post-extubation prophylactic NIV (on the day of extubation and the following day): categorical variable. Yes or no
    - In case post-extubation prophylactic NIV:
      - Per-protocol: categorical variable. Yes or no
        - If per protocol, reason(s) for NIV

SBT-TP failure (for intervention group): categorical variable. Yes or no

Age>65 years old: categorical variable. Yes or no

COPD: categorical variable. Yes or no

Chronic heart failure: categorical variable. Yes or no

Chronic respiratory failure: categorical variable. Yes or no

PaCO2>45mmHg at the end of SBT: categorical variable. Yes or no

- - - - - Duration of NIV: continuous variable. Expressed in hours, as an integer
    - In case of no prophylactic NIV:
      - Reason: categorical variable. Per protocol, violation of protocol or contra-indication

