5.2.4 Daily assessments

Multiple analyses will be performed (methodology described in 5.1)

1. Description of daily assessments for the successful extubation.

The population of analysis will be patients that were successfully extubated. We will report (cf. 4.3):

- - SBT data (on the day of extubation)
  - extubation data
    - Extubation type
    - Post-extubation prophylactic NIV characteristics. Duration of NIV will be computed as the sum of NIV duration on the day of extubation and the following day
    - Post-extubation rescue NIV (during the 7 days following extubation
    - Post-extubation high-flow nasal oxygen (during the 7 days following extubation)
    - Respiratory physiotherapy (during the 7 days following extubation)

Results will be reported a table with four columns (intervention group, control group, p-value).

1. Description of reintubation episodes:

The population of analysis will be patients that experienced reintubation. Since patients can experience multiple reintubations, we will report the number of patients involved and the total number of reintubation. We will not correct for repeated measures. We will report:

- Reintubation data (cf. 4.3)
- Time elapsed since extubation: continuous variable (hours), equals to date/time of reintubation minus date/time of extubation

Results will be reported a table with four columns (intervention group, control group, univariable absolute difference with 95% confidence interval, p-value).

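### Secondary outcome 3 is defined as cumulative time on invasive and non-invasive ventilation but computed as elapsed time since inclusion, so hours off ventilation can be counted as ventilation

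*Protocol*

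**What the plan says.** Protocol section 4.2 lists two ventilation-duration outcomes side by side.

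- Item 2 (invasive ventilation) is a sum of episodes: "Each time period spent on invasive mechanical ventilation from inclusion until successful extubation are summed up".
- Item 3 (invasive and non-invasive ventilation) is introduced as "total cumulative time spent on invasive and non-invasive mechanical ventilation since inclusion per group". Its bullets then give the calculation. With NIV: "If the patient is successfully extubated with post-extubation NIV: date/time of NIV cessation minus date/time of inclusion", with ICU discharge standing in when NIV is still running at that point. Without NIV: "If the patient is successfully extubated without post-extubation NIV: date/time of successful extubation minus date/time of inclusion". Patients who are never successfully extubated are censored at Day 90 or at death.

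The primary outcome in section 4.1 is also an elapsed time: "The primary outcome will be duration (in hours) between study inclusion and successful extubation". Success is "defined by the absence of reintubation or death within the 7 days (168 hours) following extubation".

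Item 3 serves secondary objective 3 in section 1.2, which asks about the duration of both kinds of ventilation together. Section 5.2.1.2 sends all secondary outcomes to the general methods of section 5.1. Nothing elsewhere in the protocol changes the item 3 calculation.

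**The concern.** The sentence that names item 3 and the bullets that compute it describe different quantities. No bullet removes time spent breathing without support, either between a failed extubation and the reintubation or between NIV sessions. An analyst who follows the bullets counts those hours as ventilation. Items 2 and 3 open with the same kind of phrase but sit on different scales, so a reader of the results table would naturally, and wrongly, take the difference between them as NIV time.

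At stake is objective 3: it would be reported as ventilation duration but answered with time to the end of ventilation. The affected patients are not exotic in this population. Everyone enrolled has already failed one T-piece trial, and section 5.2.4 provides for repeated failures: "Since patients can experience multiple reintubations, we will report the number of patients involved and the total number of reintubation".

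**Working it through.** The protocol states no figure for this outcome, so there is nothing to reproduce. The check compares the definition with the rule.

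**Notation** (hours since inclusion, for a patient who is eventually successfully extubated)

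- S = time of successful extubation; N = time of NIV cessation (or ICU discharge)
- I = sum of invasive periods up to S (this is item 2)
- G = total time between failed extubations and reintubations, so S = I + G
- V1 = NIV hours inside those gaps; V2 = NIV hours after S

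**Formulas**

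- Definition: I + V1 + V2
- Rule: N with post-extubation NIV, S without
- Over-count without NIV after S: S − I − V1 = G − V1
- Over-count with NIV after S: (G − V1) + (N − S − V2)

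The over-count is therefore the unsupported time in the gaps plus the unsupported time between NIV sessions. Because failure by reintubation is judged over 168 h, each failed extubation can contribute up to about 168 h, less any NIV given in that interval.

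**Illustrations.** All timelines are assumed; the protocol gives neither gap lengths nor NIV session hours.

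| Case | Ventilated time (definition) | Rule | Over-count |
|---|---|---|---|
| A. Invasive 48 h, gap 24 h, invasive 96 h, no NIV | 48 + 96 = 144 h | 48 + 24 + 96 = 168 h | 24 h |
| A. Same, gap 96 h | 144 h | 48 + 96 + 96 = 240 h | 96 h |
| A. Same, gap 167 h | 144 h | 48 + 167 + 96 = 311 h | 167 h |
| A. Gap 96 h with 16 h of NIV in it | 144 + 16 = 160 h | 240 h | 80 h |
| B. Success at 48 h, NIV stopped at 96 h, 8 h on NIV | 48 + 8 = 56 h | 96 h | 40 h |
| B. Same, 16 h on NIV | 64 h | 96 h | 32 h |
| B. Same, 24 h on NIV | 72 h | 96 h | 24 h |
| B. Same, NIV continuous for 48 h | 96 h | 96 h | 0 h |
| C. One extubation at 48 h, successful, no NIV | 48 h | 48 h | 0 h |

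In case A without NIV, item 2 is 144 h throughout, while item 3 equals the primary outcome. With the 96 h gap, the patient shows 96 h more on item 3 than on item 2 without having received any NIV.

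**Can the defined quantity be built from the planned data?** Only in part. Section 4.3 lists "Duration of NIV: continuous variable. Expressed in hours, as an integer" under prophylactic NIV, which covers two calendar days starting with the extubation day. Rescue NIV is recorded as a category, without hours. By contrast, the study procedure table (section 2.6) does collect the date and hour at which invasive ventilation and NIV cease, so the rule can be computed as written.

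**Does the planned test fit the rule?** Item 3 censors patients who are never successfully extubated. Section 5.1 provides the Mann-Whitney test and Hodges-Lehmann differences for quantitative variables, and neither accommodates censored values.

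**The case against.** The best defence is that the bullets are an explicit, complete rule: they cover NIV, no NIV, NIV still running at ICU discharge, and no success. Elapsed time is also how the protocol defines the primary outcome and the day count in ventilator-free days, so item 2 is the exception and item 3 may simply carry a loose label. This largely stands, and it is why renaming is the natural remedy. It does not remove the contradiction, because the label and the objective still promise a quantity that the rule does not deliver.

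It is also fair that the illustrations are assumed, that NIV given inside a gap shrinks the over-count, that many patients will have none, and that no planned analysis subtracts item 2 from item 3. The prophylactic NIV hours are complete for that NIV as the protocol defines it; what lacks hours is rescue and prolonged NIV.

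A reader might infer that the error works against the intervention arm, because a failed T-piece trial is an additional NIV trigger there and secondary objective 8 mentions a higher reintubation rate. The protocol does not support that. Objective 8 asks whether reintubation is higher; it does not predict it. Objective 1 asks whether first extubation succeeds more often under the assisted strategy, which would mean fewer gaps in that arm. The two arms share every other NIV criterion, and no reintubation rate is assumed for either.

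**Conclusion.** The point holds as an inconsistency between definition and calculation in one secondary outcome. For successfully extubated patients with an earlier failed extubation or intermittent NIV, the rule counts unsupported time as ventilation. The over-count is zero for one uninterrupted course. In the assumed cases with interruptions it runs from 24 to 167 h per patient. For scale, section 2.5 regards 24 h as a relevant between-arm difference in time to extubation, but the figures here are individual over-counts, not group differences. The share of patients affected, and the size and direction of any effect between arms, cannot be determined from the protocol. The primary outcome and the sample size are not touched. The plan should be corrected, and the cost is small.

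**What to change.** **Preferred.** Rename item 3 and secondary objective 3 as *time from inclusion to liberation from all ventilation (invasive and NIV)* and keep the present rule, stating that ICU discharge stands in for cessation when NIV is still running. Exempt item 3 from the section 5.1 tests and analyse it as time to event, because of its own censoring rule. The approach already planned for the primary outcome in section 5.2.1.1 could be reused. Cost: wording in sections 1.2, 4.2 and 5.2.1.2; no new data.

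**Alternative.** If cumulative ventilated time is what is wanted, define item 3 as item 2 plus the summed NIV hours, and replace the elapsed-time bullets. This requires recording NIV hours, including rescue NIV, beyond the extubation day and the next day, through to NIV cessation. Cost: a few case report form fields, and hours that may be hard to recover for patients already followed.
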